### Plans for collection, laboratory evaluation, and storage of biological specimens for genetic or molecular analysis in this trial/future use {33}

This is not applicable, as there are no plans for the collection, laboratory evaluation, or storage of biological specimens for genetic or molecular analysis in this trial or for future use in ancillary studies.

## Statistical methods

### Statistical methods for primary and secondary outcomes {20a}

Baseline patient characteristics will be presented according to the by aftertreatment regime. Continuous variables will be summarized using either mean and standard deviation or as median and interquartile range. Categorical variables will be summarized as count and percentages.

All analyses of the primary and secondary study parameters will be conducted following both the intention-to-treat principle and the per-protocol principle. Statistical significance will be determined using a *p*-value of ≤ 0.05. All analyses will be carried out using “R” or IBM SPSS version 28 or later.

#### Primary study parameter

For the primary research question, the AOFAS Score at 6 months, a continuous outcome, will be utilized. The relative effectiveness of PWB compared to RWB on the AOFAS score will be analyzed using a linear regression model. The model will be adjusted for the type of surgery and hospital. The objective is to assess the non-inferiority of PWB compared to RWB, with a non-inferiority margin set at 5 points. To evaluate non-inferiority, a two-sided hypothesis test will be conducted to determine whether the lower limit of the confidence interval for the estimated treatment effect exceeds the predefined non-inferiority margin. The corresponding p-value for non-inferiority will be calculated using the input from the estimated model. The assumptions for the linear regression model will be evaluated, including linearity, independence of errors, homoscedasticity, and normality of residuals.

#### Secondary study parameters

The MFS score at 6 months will be analyzed using a linear regression model to compare between the PWB and RWB groups, similar to the analysis of the primary study parameter. EQ-5D scores at 6 months will be compared between groups using a linear mixed-effects regression model to account for clustering of multiple observations within each patient. Both absolute differences between groups, as well as the difference in slope over time will be estimated. All parameters will be reported, including 95% confidence interval. Binary secondary outcome variables (i.e., having received any secondary surgical procedure, experienced any type of complication, showing differences on radiographs) will be compared between groups using logistic regression analysis.

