### Intervention description {11a}

#### Permissive weight bearing

The PWB protocol represents a relatively new approach to early weight bearing, enabling earlier postoperative weight bearing. Progression of weight bearing is determined by the patient’s subjective experience, such as pain levels and weight bearing tolerance, along with the clinical expertise of the treating physician and physiotherapist, in line with the PROMETHEUS protocol [12]. The rehabilitation regimen commences with 2 weeks of immobilization to facilitate wound healing. Subsequently, patients are allowed to bear as much weight as tolerated, guided by their pain levels and comfort [12].

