#### Restrictive weight bearing

The RWB protocol adheres of 8 to 12 weeks of postoperative weight bearing restriction, in the range of 0–10%, so-called *touching load*, as outlined in the current AO Guidelines [16]. Following this initial phase, which entails restricted weight bearing, a gradual increase in weight bearing is implemented. This entails a weekly increment of 25% over the course of 4 weeks. During each patient-physician encounter, the weight bearing advice provided to the patient is meticulously recorded. This includes whether the recommendation is for unloaded, partial weight bearing with clarification, or full weight bearing. Furthermore, any additional advice imparted to the patient is also documented.

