#### Secondary outcomes

Secondary outcomes encompass several measures.The Maryland Foot Score (MFS): The MFS is a tool for assessing foot disorders, comprising evaluations of pain, gait, functional activities, and cosmesis. Scores range from 0 to 100 points, with < 50 indicating poor, 50–74 as fair, 75–89 as good, and 90–100 as excellent outcomes [22]. Time points: collected at 2 weeks, 6 weeks, 12 weeks, and 6 months post-surgery.Health-related quality of life (HRQoL) using the EuroQoL 5-Dimension 5-Level (EQ-5D-5L): This self-administered questionnaire comprises five dimensions (mobility, self-care, daily activities, pain/discomfort, and depression/anxiety), each rated on five levels. Utilities calculated using preferences from the Dutch tariff will enable Quality Adjusted Life Years (QALY) scoring, besides the questionnaire is recommended by the Dutch guidelines [23, 24]. Time points: collected at baseline, 2 weeks, 6 weeks, 12 weeks, and 6 months post-surgery.Radiographical characteristics: Evaluation of Böhlers angle and posterior facet joint alignment via radiographic assessment by a blinded radiologist will be conducted at scheduled physician visits. CT scans early post-operatively and at 6 months will be used to measure differences in Böhlers angle and posterior joint alignment [25]. Differences in the Böhlers angle and posterior joint alignment (Δ = CT_6months_—CT_post-op._) will be calculated. Normal Böhlers angle ranges between 25° and 40° [26]. Intra-articular step-off or gap < 2 mm of the posterior facet is considered well-reduced [3]. Time points: early post-operative (‘baseline’) and at 6 months post-surgery CT scan.Medical consumption and productivity: Measured using the Medical Consumption Questionnaire (iMCQ) and Productivity Costs Questionnaire (iPCQ). The iMCQ assess healthcare utilization, while the iPCQ captures productivity losses. The iPCQ and iMCQ are generic and complimentary questionnaires, that can be used in every indication and are adapted to the context of this study [27]. Time points: collected at baseline, 12 weeks, and 6 months post-surgery.Total complication rate: A wound infection is defined as (but not limited to) purulent wound drainage, inflammation, erythema, fever, increased white blood cell count, increased C-reactive protein and/or increased erythrocyte sedimentation rate, necessitating admission for antibiotic treatment and/or revision surgery for infection.A dislocation is defined as the migration of fracture parts, defined as >3 mm articular step-off or gap and/or varus/valgus malalignment > 5° after weight bearing. A non-union is defined as no radiographic union achieved after 6 months or no progress in healing. Failure of osteosynthesis is defined as loosening or breakage of implants, including the rate of reoperation (e.g., leading to removal of material, arthrodesis). Postoperative arthritis will be screened on CT scans. Time points: evaluated at 2 weeks, 6 weeks, 12 weeks, and 6 months post-surgery.

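### The EQ-5D analysis targets 6 months, but the group difference and slope difference it names as outputs need not equal the 6-month difference

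*Protocol article*

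**What the plan says.** In the protocol article, Secondary study parameters fixes the target and the type of model: "EQ-5D scores at 6 months will be compared between groups using a linear mixed-effects regression model". The stated reason for the mixed model is that each patient contributes several observations. The next sentence names what will be reported: "Both absolute differences between groups, as well as the difference in slope over time will be estimated". No time point is attached to the absolute differences, and the section does not mention how baseline EQ-5D is used.

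Secondary outcomes gives the EQ-5D schedule: "collected at baseline, 2 weeks, 6 weeks, 12 weeks, and 6 months post-surgery". That is five visits.

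For the permissive arm, Intervention description states: "The rehabilitation regimen commences with 2 weeks of immobilization". The restrictive arm is held to touch load for 8 to 12 weeks and then progressed over 4 weeks. Trial design says that secondary outcomes are assessed for superiority.

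**The concern.** The target is a difference at one time point. The named outputs are a difference with no time point and a rate of change. The Maryland Foot Score sentence just before it uses ordinary regression on the 6-month score, which gives its target directly. The EQ-5D sentence does not.

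The early visits make this matter. Permissive loading has not begun before week 2, so no loading-driven difference is expected at baseline or week 2. A group term that pools these visits with later ones, or a straight line forced through all of them, mixes visits without a contrast into a result that will be read as the 6-month effect. Analysts could follow the text faithfully and report different numbers for the trial's health-related quality-of-life outcome, depending on how they code time.

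**Working it through.** **The plan's own figure.** No EQ-5D figure is given. The only sample size rests on the AOFAS score: 2 × (1.96 + 0.84)² × 8.5² / 5² = 45.3, so 46 per group and 92 in total; 92 / 0.8 = 115. It reproduces and does not depend on this point.

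**Inputs.** From the documents: visits at 0, 2, 6 and 12 weeks and 6 months (taken as 26 weeks), and permissive loading starting after week 2. Assumed: the pattern of true between-group differences, complete data, and a random intercept (equal within-patient correlation). With complete data and this correlation structure, generalised least squares equals ordinary least squares on the visit-specific differences. The results were identical for correlations of 0.3, 0.5 and 0.7.

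**Formulas.** Let d be the vector of true differences at the five visits.

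- All-visit group term: the mean of d.
- Linear time-by-group model: mean visit time = 46/5 = 9.2 weeks; deviations −9.2, −7.2, −3.2, 2.8, 16.8; sum of squares 436.8. Slope b = Σ(deviation × d) / 436.8. Fitted difference at 26 weeks = mean(d) + 16.8b; at time zero = mean(d) − 9.2b.
- Group by categorical visit: the contrast at 26 weeks is the last element of d.

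**Worked example, constant effect from week 6,** d = (0, 0, 1, 1, 1): mean = 0.60. b = (−3.2 + 2.8 + 16.8) / 436.8 = 0.0375. At 26 weeks: 0.60 + 16.8 × 0.0375 = 1.23. At time zero: 0.60 − 9.2 × 0.0375 = 0.25.

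| Assumed pattern d | True at 26 wk | All-visit group term | Linear, at 0 wk | Linear, at 26 wk | Group-by-visit, 26 wk |
|---|---|---|---|---|---|
| Constant from week 6 (0, 0, 1, 1, 1) | 1 | 0.60 | 0.25 | 1.23 | 1.00 |
| Equal steps (0, 0, 1/3, 2/3, 1) | 1 | 0.40 | 0.03 | 1.08 | 1.00 |
| Linear from week 2 (0, 0, 4/24, 10/24, 1) | 1 | 0.32 | −0.05 | 0.99 | 1.00 |
| Converged by 6 months (0, 0, 1, 1, 0) | 0 | 0.40 | 0.41 | 0.38 | 0.00 |

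The last row is possible on the protocol's own timetable: restriction of 8 to 12 weeks plus 4 weeks of progression ends at 12 to 16 weeks, well before 26.

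**On the EQ-5D scale.** With an assumed effect of 0.06 from week 6, the first row gives 0.60 × 0.06 = 0.036 for the group term and 1.23 × 0.06 = 0.074 for the linear model. In the last row, with 0.06 at weeks 6 and 12 only, the linear model reports 0.38 × 0.06 = 0.023 where the truth is 0.

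**If baseline is not modelled as an outcome.** Week 2 still precedes the contrast. For d = (0, 1, 1, 1) at weeks 2, 6, 12 and 26, the group term is 3/4 = 0.75. For the linear model, mean time is 11.5 weeks, the sum of squares is 331 and b = (−5.5 + 0.5 + 14.5) / 331 = 0.0287, giving 0.75 + 14.5 × 0.0287 = 1.17 at 26 weeks. The mismatch shrinks but stays.

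**Baseline adjustment.** With correlation r between baseline and 6-month EQ-5D, the variance of the adjusted 6-month contrast is about (1 − r²) times the unadjusted one. For r = 0.3, 0.4 and 0.5 the saving is 9%, 16% and 25% in variance. In standard error it is 1 − √0.91 = 5%, 1 − √0.84 = 8% and 1 − √0.75 = 13%. The values of r are assumed.

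**The case against.** The text does not say which visits enter as outcomes, how time is coded, or that the absolute difference is a single group term. The sentence does name 6 months, and its plural wording for the differences is compatible with visit-specific contrasts. With time centred at 6 months, even the group term of an interaction model is a fitted 6-month difference. A group-by-visit model, or one with a common baseline mean, recovers the 6-month value exactly with baseline and week 2 included. Time coding and covariates are also matters that a condensed article commonly leaves to the full protocol or analysis plan.

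Most of this stands. A reader might infer that the early visits are certainly modelled, that the reported difference therefore is not the 6-month one, that the effect is understated, and that baseline EQ-5D goes unused. The documents support none of these as fact. Understatement fails even as a direction: a slope term is planned, and the linear model overstates in the first two patterns of the table.

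What remains is narrower. The article does not leave the outputs open. It names them, and neither is tied to the stated target. Centring time does not cure the linear model, because the 1.23 and 0.38 are its fitted values at 26 weeks whatever the origin.

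**Conclusion.** The point holds as a mismatch between the stated target and the stated outputs, on one secondary outcome. Under the literal readings with all five visits, the reported value is 0.32 to 0.60 of the 6-month difference for a group term and 0.99 to 1.23 of it for a linear model. When the true 6-month difference is zero, either reading reports about 0.4 of the earlier effect. The direction depends on the effect pattern and the coding, so no general claim of under- or overstatement is justified.

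The figures rest on assumed patterns with no difference at baseline and week 2, on complete data and on a random intercept. In an open-label trial, knowing the allocation could shift EQ-5D at week 2, so the zero there is an assumption too. That the article states no baseline adjustment is a missed gain in precision, not an error. The AOFAS analysis and the 46 / 92 / 115 figures are untouched.

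**What to change.** In Secondary study parameters, specify the EQ-5D model as post-baseline EQ-5D with categorical visit, group, group-by-visit and baseline EQ-5D as a covariate. An equivalent choice is to keep baseline as an outcome with one common mean for both arms. State that the reported between-group difference is the model contrast at 6 months with its 95% confidence interval, and that the slope difference is supportive only.

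The cost is a wording change before analysis. Baseline EQ-5D is already collected, so no new data are needed. The small downside is a few more parameters: four visit-specific differences in place of one intercept and one slope difference.

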### Introduction

#### Background and rationale {6a}

Fractures of the calcaneus constitute up to 2% of all fractures and account for 60% of all fractures of the foot. Among calcaneal fractures, approximately 65% are intra-articular [1]. Surgical intervention is frequently required to restore the subtalar joint and the anatomical shape of the calcaneus. Given that calcaneal fractures predominantly affect middle-aged males, their socio-economic ramifications are considerable [2–5]. Approximately 20% of patients will not return to work within 1 year after injury [6]. Hence, post-fracture rehabilitation plays a pivotal role in the management of calcaneal fractures.

“The PermIssive Or Non wEight bEaRing in calcaneal fractures study” (the PIONEER study) will be the first prospective randomized controlled trial (RCT) comparing two rehabilitation protocols. Increasing evidence suggests that early weight bearing protocols such as permissive weight bearing (PWB), reduce the time to full weight bearing without adversely affecting patient-reported quality of life, pain levels, or complication rates [7, 8]. The greatest benefits of early weight bearing in lower extremity fractures are believed to be realized within the initial 6 months post-surgery [9]. Additionally, a recent systematic review on calcaneal fractures indicates that Early Weight Bearing (EWB) may not lead to inferior outcomes compared to the current, more conservative, weight bearing regimes [10]. Presently, both non-weight bearing (NWB) and EWB protocols are utilized in Dutch hospitals for calcaneal fractures [11]. However, a prospective study comparing these two rehabilitation protocols in displaced intra-articular calcaneal fractures (DIACFs) is lacking. Furthermore, there is a paucity of research comparing complication rates between the two protocols in the aftertreatment phase of DIACFs. Consequently, the safety of EWB following surgery in patients with DIACFs remains uncertain.

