### Provisions for post-trial care {30}

The sponsor maintains liability insurance in accordance with article 7 of the Medical Research Involving Human Subjects Act (WMO). Aftertreatment following the PWB protocol is already implemented in several hospitals in the Netherlands, including for DIACFs. While no adverse effects have been noted from clinical experience, there may be potential risks that are currently unknown. Additionally, a recent retrospective study, not yet published, and a systematic review and meta-analysis reported no negative effects on patients’ reported quality of life, pain, or complication rates.

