### Sample size {14}

To our knowledge, there is no literature available that directly compared our primary outcome (AOFAS Score) in PWB versus RWB for surgically treated patients with DIACFs. Therefore, unfortunately, the MCID is unknown for the AOFAS Score [28, 29].

However, the estimated minimal clinical difference (MCID) can be calculated as one half of the standard deviation (0.5 SD) [30]. Preliminary results of a systematic review that is currently performed by our group, found a mean AOFAS Score of 83.7 (SD 8.5) for the RWB group. 0.5 × 8.5 results in a MCID of 4.3, respectively.

Besides, a recent Cochrane review reported a MCID for the AOFAS Score in other foot conditions that range from 2.0 to 7.9 [29]. This results in a mean MCID of (2.0 + 7.9)/2 = 5, respectively.

For this sample size calculation, a MCID of 5 points was assumed, approximating a 0.5 SD of the estimated mean AOFAS score after RWB for surgically treated patients with DIACFs [30].

In order to be able to detect such a difference between the two groups, assuming that an equal number of patients in both groups will be included, with an alpha of 5% and beta of 20% (power 80%), a pooled SD of 8.5 and a true difference of zero points between the RWB and PWB group the sample size should be at least 46 for both groups = 92 in total. Anticipating a 20% drop out a total of 115 patients must be recruited for this study. The sample size calculation was performed with a two-sample mean test for non-inferiority using the TrialSize package within “R.”

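### Binary secondary outcomes are assigned to logistic regression with no small-sample method named; if RWB risk is about 5% or less, default Wald inference would be unusable or clearly conservative

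*Protocol article*

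**What the plan says.** The protocol article, under Secondary study parameters, lists the binary outcomes and their analysis in one sentence: "having received any secondary surgical procedure, experienced any type of complication, showing differences on radiographs) will be compared between groups using logistic regression analysis". It does not state an estimator (maximum likelihood, penalised or exact), a test (Wald, likelihood ratio) or covariates for this model.

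Statistical methods {20a} adds the decision rule, "Statistical significance will be determined using a *p*-value of ≤ 0.05", and names R or SPSS as software. Trial design {8} places secondary outcomes in a superiority frame.

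The numbers available come from Sample size {14}: "the sample size should be at least 46 for both groups = 92 in total", raised to 115 recruited for 20% dropout. That calculation concerns the AOFAS score only. No event rate or power is given for any binary outcome.

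**The concern.** Secondary surgery is one of the outcomes on which mechanical harm from earlier loading would show. Background and rationale {6a} says "there is a paucity of research comparing complication rates between the two protocols in the aftertreatment phase of DIACFs" and treats the safety of early weight bearing as an open question.

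With about 50 patients per arm, a 2% to 5% risk means one to three expected events per arm. In that range the usual software output for logistic regression, a maximum-likelihood odds ratio with a Wald p-value, behaves poorly. With no event in one arm the estimate diverges, and the p-value goes to 1 however many events the other arm has. With one or two events the fit looks normal, but the test rejects far less often than its nominal 5%. Different tests that all count as logistic regression then give different answers on the same table, and the text does not say which one decides.

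**Working it through.** **Inputs.** From the document: 46 evaluable patients per arm, 115 recruited at 1:1 (57 v 58), p ≤ 0.05. Assumed, because the document gives no rates: RWB risk 1% to 15%, PWB risk 10% to 30%. All calculations are unadjusted, since no covariates are stated for this model.

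**Sample size reproduced.** n per arm = 2(1.960 + 0.842)² × 8.5² / 5² = 45.4, so 46 per arm and 92 in total; 92 / 0.8 = 115. The stated figures are correct.

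**Empty arm.** P(no event in an arm of n) = (1 − p)ⁿ. For one arm of 58: 31% at 2% risk, 5.1% at 5%, 0.2% at 10%. For one arm of 46: 39% at 2%, 9.4% at 5%, 0.8% at 10%. The chance that at least one of the two arms is empty, with equal risks, is 53% at 2% and 10% at 5% (57/58), or 63% and 18% (46/46).

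**Example, PWB 6/57 v RWB 0/58.** The maximum-likelihood fit gives log odds ratio 22.4, SE about 17,200, Wald p = 0.999. N-1 chi-square = (6×58 − 51×0)² × 114 / (57×58×6×109) = 6.39, p = 0.011. Firth p = 0.011, Fisher p = 0.013, likelihood-ratio p = 0.003.

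**Example, PWB 7/57 v RWB 1/58.** Log odds ratio = ln(7×57 / (50×1)) = 2.08; SE = √(1/7 + 1/50 + 1/1 + 1/57) = 1.09; Wald p = 0.056. Firth p = 0.028, N-1 p = 0.027, Fisher p = 0.032. Nothing in this fit looks broken.

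**Exact enumeration.** The binomial probabilities of all 2×2 tables were summed over those rejected at 0.05; an empty cell counts as no rejection for Wald.

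Type I error at 57/58, equal risk in both arms:

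| Risk | Wald | Likelihood ratio | Firth | N-1 |
|---|---|---|---|---|
| 5% | 0.4% | 8.3% | 3.5% | 5.1% |
| 10% | 2.9% | 5.8% | 4.5% | 5.0% |
| 15% | 4.0% | 5.2% | 4.8% | 5.1% |

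Power at 57/58:

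| PWB v RWB | Wald | Firth | N-1 | Fisher |
|---|---|---|---|---|
| 10% v 1% | 8% | 60% | 65% | 51% |
| 10% v 2% | 10% | 43% | 50% | 37% |
| 15% v 2% | 37% | 75% | 79% | 71% |
| 15% v 5% | 33% | 43% | 46% | 39% |
| 20% v 5% | 62% | 70% | 73% | 68% |
| 25% v 10% | 54% | 57% | 58% | 54% |
| 30% v 15% | 47% | 49% | 49% | 47% |

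At 46/46, Wald, Firth and N-1 power is 19%, 35% and 36% for 15% v 5%; 45%, 61% and 62% for 20% v 5%; and 45%, 47% and 49% for 25% v 10%.

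**The case against.** The strongest reply is that the document does not contain this error.

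- **No Wald test is specified.** Likelihood-ratio and Firth inference are also logistic regression, and an SE of 17,000 would alert any analyst. This stands: the failure belongs to a software default, not to a stated test. But the 7/57 v 1/58 example gives no such warning, and the text leaves open which of several differing p-values counts.
- **Rarity is assumed.** A reader might infer that the plan itself expects few events, from the remark "While no adverse effects have been noted from clinical experience" or from the abstract's mention of an acceptable complication rate. Neither supports it. The first concerns harm attributed to PWB, the second concerns other lower-extremity fractures, and neither gives a rate.
- **The listed outcomes are pooled.** Any complication and radiographic change may be common. Even reoperation is defined broadly, "including the rate of reoperation (e.g., leading to removal of material, arthrodesis", so its rate may not be low. This stands and narrows the point to whichever outcomes prove sparse. Individual complication types are defined under Secondary outcomes, but the analysis sentence does not list them.
- **Much of the loss is ordinary small-sample conservatism.** At 57/58 and 15% v 5%, Fisher has 39% power against 33% for Wald; at 46/46, 1 v 7 events gives 0.059 and 0.056. This is correct, but Fisher is itself conservative. Firth and N-1 do better without the likelihood-ratio test's inflation.
- **Test choice can be left to the analysis plan.** It can, and the absence of that detail is not the complaint. The protocol does fix the method family for these outcomes, and a better one for sparse data can be named at almost no cost.

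**Conclusion.** The point holds conditionally. If the RWB risk of an outcome is about 5% or less, default Wald inference is unusable with an empty arm and clearly conservative otherwise. At 15% v 5% it gives up about 14 percentage points of power against N-1 chi-square at 57/58 (32.5% v 46.2%) and about 17 at 46/46 (18.9% v 35.7%). The loss is far larger at RWB risks of 1% to 2%. By 10% it is about 4 points, and by 15% about 2 points or less.

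This rests on assumed event rates, an unadjusted model and use of the default Wald output. A reader might conclude that the planned analysis breaks down, or would hide a clear excess of reoperations under PWB. The document does not support that, because it states neither the test nor rates low enough to cause it. Nor can hospital adjustment be read into this model: it is stated for the AOFAS score, and by analogy for the Maryland Foot Score, but not for binary outcomes. What remains is a modest, inexpensive improvement to make before results are seen.

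**What to change.** Under Secondary study parameters, state that binary outcomes will be analysed by Firth-penalised logistic regression with penalised-likelihood tests and intervals. Report alongside it the risk difference (PWB minus RWB) with a Miettinen-Nurminen or Newcombe 95% CI. An N-1 chi-square p-value is an acceptable unadjusted alternative, but one test should be named as the one that decides.

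The cost is one sentence and routine software functions, with no extra patients or data. Penalisation changes little when events are common, so the same rule can cover every binary outcome. The drawback is small: the simple risk difference carries no covariate adjustment. In return it shows the absolute excess risk, which an odds ratio does not.

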**Fig. 1 Fig1:**
[figure not shown]
Schematic overview of the consequences of loading on the consolidation

Currently, the AO (*Arbeitsgemeinschaft für Osteosynthesefragen*) protocol for postoperative management of DIACFs involves NWB for 8 to 12 weeks, followed by a weekly 25% increment in weight loading [16]. Despite the well-established positive impact of early weight bearing on fracture healing and preservation of muscle and bone mass, this regimen has remained the standard for decades [17]. Consequently, there arises a question as to whether physicians and physiotherapists may be overly cautious, driven by concerns about secondary fracture displacement or mechanical construct failure.

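### Complications are compared between arms only as any complication, which mixes mechanical failure with other events and would mute a mechanical harm of early loading

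*Protocol article*

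**What the plan says.** The background to the protocol article asks whether current practice is over-cautious, "driven by concerns about secondary fracture displacement or mechanical construct failure". The objectives include comparing complication rates, and the closing discussion says that the trial will establish the safety of both regimens.

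Under Statistical methods {20a}, Secondary study parameters, three binary outcomes are listed after an i.e., so the list reads as closed: "having received any secondary surgical procedure", "experienced any type of complication" and "showing differences on radiographs". These "will be compared between groups using logistic regression analysis". The Trial design section places secondary outcomes on a superiority footing.

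Under Outcomes {12}, Secondary outcomes, the total complication rate is built from:
- wound infection needing admission for antibiotics and/or revision surgery;
- dislocation, with thresholds for step-off or gap (more than 3 mm) and malalignment (more than 5°);
- non-union;
- failure of osteosynthesis, meaning implant loosening or breakage, "including the rate of reoperation (e.g., leading to removal of material, arthrodesis";
- arthritis: "Postoperative arthritis will be screened on CT scans".

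Complications are evaluated at 2, 6 and 12 weeks and at 6 months. For the permissive arm, "The rehabilitation regimen commences with 2 weeks of immobilization to facilitate wound healing". The same section also makes the change in Böhler's angle and posterior facet alignment between the post-operative and 6-month CT a secondary outcome, with radiographic assessment by a blinded radiologist.

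**The concern.** A patient counts once in an any-complication variable. Someone already positive through infection, arthritis or a reoperation adds nothing further if the fracture also displaces. Events that occur at similar rates in both arms therefore dilute the events that loading could cause.

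The direction matters because the comparison is a superiority test. Dilution moves the result towards no difference, which is the answer that favours permissive weight bearing. The plan has no interim analysis and no data monitoring committee, so the final comparison carries much of the formal safety evidence. The dislocation thresholds, the most specific mechanical definition in the document, enter a listed binary analysis by name only through the pooled variable.

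**Working it through.** **The plan's own figure.** The only calculated size is for the AOFAS score: SD 8.5, margin 5, true difference 0, power 80%. With one-sided alpha 0.025, n = 2 × (8.5 × (1.960 + 0.842) / 5)² = 45.4, so 46 per arm and 92 in total. Allowing for 20% drop-out, 92 / 0.8 = 115. This reproduces. No complication rate or power for complications is stated.

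**Inputs for the illustration.** From the protocol: n = 46 per arm and a 5% significance level. Assumed: mechanical rate m₁ = 5% under restricted and m₂ = 15% under permissive weight bearing, and a background rate b of other complications that is equal in both arms and independent of mechanical events.

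**Formulas.**
- Pooled rate: c = 1 − (1 − m)(1 − b). The difference between arms becomes (1 − b)(m₂ − m₁).
- Power, two-sided 5%: Φ[(d − 1.96·√(2p̄(1 − p̄)/n)) / √((p₁(1 − p₁) + p₂(1 − p₂))/n)], with p̄ the mean of the two rates.

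**Worked case, b = 10%.** c₁ = 1 − 0.95 × 0.90 = 0.145 and c₂ = 1 − 0.85 × 0.90 = 0.235, so d = 0.09 and p̄ = 0.19. The null standard error is √(2 × 0.19 × 0.81 / 46) = 0.0818 and the alternative one is 0.0813. Power = Φ[(0.09 − 0.1603) / 0.0813] = Φ(−0.87), or about 19%.

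| Background | Rates compared | Difference (points) | Odds ratio | Power |
|---|---|---|---|---|
| none (mechanical alone) | 5.0% v 15.0% | 10 | 3.35 | 36% |
| 10% | 14.5% v 23.5% | 9 | 1.81 | 19% |
| 20% | 24.0% v 32.0% | 8 | 1.49 | 13% |
| 30% | 33.5% v 40.5% | 7 | 1.35 | 10% |
| 40% | 43.0% v 49.0% | 6 | 1.27 | 8% |

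**Other assumed mechanical rates, 46 per arm, background 10% to 40%.**
- 5% v 10%: power 15% alone, 8% to 5% pooled.
- 5% v 20%: power 59% alone, 35% to 14% pooled.
- 5% v 25%: power 78% alone, 53% to 21% pooled.

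With 57 per arm (all 115 recruited, no loss), 5% v 15% gives 43% alone and 23% to 9% pooled.

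**Small-sample check.** At 5% v 15% the expected mechanical events are 46 × 0.05 = 2.3 and 46 × 0.15 = 6.9, so the normal approximation is optimistic. Fisher's exact test gives 24% for mechanical events alone.

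**Precision after separating the events.** At 5% v 15% the 95% interval for the risk difference is about 10 ± 1.96 × √((0.0475 + 0.1275)/46) = 10 ± 12.1 points. With 5% in both arms it is 0 ± 1.96 × √(2 × 0.0475/46) = 0 ± 8.9 points.

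**The case against.** The strongest reply is that mechanical harm has other routes to detection. The CT change in Böhler's angle and facet alignment measures loss of reduction directly in every patient with both scans, and infection or hardware removal cannot mask it. Reoperation and radiographic differences are analysed separately in the same sentence as complications. This stands, and a reader should not infer that the trial has only one safety variable or could not show a mechanical harm. The routes are partial, however: the CT change does not capture implant breakage or non-union, secondary surgery can include revision for infection, and no threshold is given for the radiographic variable.

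Three further inferences go beyond the text:
- That removal of intact, irritating hardware counts as construct failure. The definition can equally be read as reoperation because of loosening or breakage. It is ambiguous, not stated.
- That pre-existing joint change counts as arthritis. The article speaks of postoperative arthritis, and of post-traumatic arthritis in the data management section. What it lacks is a grade and a stated comparison with the post-operative CT. Arthritis may also follow loss of reduction, in which case it is not independent background and dilution is smaller.
- That the infections precede any contrast between regimens. Only the earliest do. Later ones could differ by regimen, and the definition already excludes minor wound problems.

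It is also fair that a total complication rate is a common secondary outcome, that tables by type may sit in an analysis plan not shown, and that separating the events does not rescue power. These points limit the weight of the finding. They do not change that the article fixes a closed list in which no binary comparison isolates the mechanical events.

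**Conclusion.** The point holds in a limited form. The stated between-arm comparison of complications is the pooled one, and no listed binary outcome brings displacement, implant failure and non-union together. If the other complications are equal between arms and independent of mechanical events, the pull towards no difference follows algebraically. Its size does not: every rate used is an assumption. In the illustration of 5% v 15% with 46 per arm, power falls from about 36% to between 19% and 8%.

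A reader might infer that the trial cannot detect mechanical harm, or that a separate mechanical endpoint would make it able to. The documents support neither. The CT outcome covers part of the question, and a mechanical comparison at this sample size stays imprecise. The primary analysis is unaffected. This is a cheap improvement to a stated safety aim.

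**What to change.** In Outcomes {12} and Secondary study parameters:
- Add one pre-specified mechanical-complication comparison: dislocation as already defined, implant loosening or breakage, non-union, and reoperation for one of these. Report it as a risk difference with 95% CI beside the total complication rate.
- State that a non-significant result is not evidence of safety.
- State that removal of intact implants is classified under secondary procedures and not under failure of osteosynthesis.
- Report arthritis as new or progressed between the post-operative and 6-month CT, and wound infection, each as a separate component.

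Cost: a few sentences of wording and one reason-for-reoperation field in the case report form. The components are already defined apart from the arthritis comparison, both CT scans are already planned, and no visit is added. The downside is few events and a wide interval.
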